## Methods

### Study Design

This project uses a 2-armed RCT design, with participants who register to be involved in the trial being randomly allocated to one of two arms: either “self-directed” completion of the *Back on Track* program or “supported” completion of the *Back on Track* program. The self-directed arm involves participants completing the web-based *Back on Track* program at their own pace without assistance. The supported arm involves the addition of 2 telephone sessions with a trained lifestyle counselor. The telephone sessions are protocol driven, with a written manual developed by a health psychologist.

Measures are assessed at three timepoints across the study: a baseline questionnaire is completed prior to participants receiving access to the web-based program, a postprogram questionnaire at the conclusion of the web-based program access (2 months after baseline), and a follow-up questionnaire 4 months later (6 months after baseline). Figure 1 shows a flowchart of the study design and the participant numbers.

An RCT design was chosen for this trial to accurately compare outcomes for the 2 modes of delivery of the web-based *Back on Track* program, either self-directed or supported. By comparing outcomes for participants in the 2 groups, we will be able to determine whether the supported approach provides benefits over and above the self-directed use of the web-based *Back on Track* program. The result will then inform the optimal form of delivery of the *Back on Track* program for future rollout to people with CHD across Australia.

**Figure 1 figure1:**
[figure not shown]
Trial design based on CONSORT (Consolidated Standards of Reporting Trials) requirements. ACHH: Australian Centre for Heart Health; PICF: participant information consent form.

### Recruitment and Participants

A total of 120 participants will be recruited into the trial, with 60 randomly allocated to each of the 2 arms of the trial. Participants will be adults (over 18 years of age) who have had an acute cardiac event, such as AMI, coronary artery bypass graft surgery (CABGS), or percutaneous coronary intervention (PCI), in the past 12 months. Participants are required to be fluent in English to comprehend the *Back on Track* program, which is currently available in English only. Participants are also required to have access to the internet and a computer or tablet.

Participants are being recruited using both direct engagement via a nationwide social media recruitment drive, and indirect engagement via cardiac health professionals and community-based cardiac support organizations, namely HeartBeat Victoria and Heart Support Australia. A promotional flyer is used for all promotion and recruitment. The nationwide social media recruitment drive involves announcements about the trial on internet-based social media platforms such as Facebook, Twitter, and LinkedIn. HeartBeat Victoria and Heart Support Australia also promote the study to their members, who are all people living with heart disease. Details of eligibility criteria are provided on the relevant websites and organization promotional material. Likewise, the trial is being promoted among cardiac health professionals, based on a list of health professionals who are involved in cardiac rehabilitation services across Australia or have attended past ACCH training programs.

In all cases of recruitment, both direct and indirect, potential participants are directed to the ACHH website for detailed information about the study and for instructions on how to register on the internet. Screening for eligibility is undertaken at the time of participant registration via the ACHH website using a set of brief screening questions; specifically, participants are asked to provide their name and contact details, type, and date of cardiac event and to confirm that they are able to read and understand English and that they have access to the internet and a computer or tablet device. All participants are asked to read, sign, and return the participant information and consent form (PICF) after registration and prior to randomization and being given program access. The PICF is emailed to participants via the secure web-based data management and survey program, Research Electronic Data Capture (REDCap), which they sign and return electronically to ACHH.

Once registered, participants are randomly allocated to either the self-directed or the supported arm of the trial using an independent and automatic random allocation numbering system. The person undertaking the random allocation is blind to group and participant details. All participants are then asked to complete the web-based baseline questionnaire, also disseminated using REDCap. The link to questionnaires is emailed to participants at each timepoint. Access to the *Back on Track* program is granted to participants for a 2-month period after they complete the baseline questionnaire.

Participants are asked to recomplete the main outcome measures again post program (2 months after initial access to the program) and at 4-month follow-up (6 months after program access). Again, the REDCap survey link is emailed to participants.

### Sample Size and Power

Our sample size is based on a systematic review of telehealth-based cardiac rehabilitation [28] on lifestyle behaviors, health outcomes, and quality of life, where the effect sizes on promoting healthy lifestyle ranged from 0.42 to 1.29. Taking a conservative approach, we expect a medium effect size of 0.55. Allowing for 80% power and a significance threshold of .05, the estimated sample size is 120 (60 per arm), which takes into consideration an expected attrition rate of 12% based on prior studies with similar posttest time points of 2-4 months [31,51].

### Intervention

#### Back on Track Program

The *Back on Track* program begins with a goal-setting module, followed by 4 self-selected modules relating to (1) healthy eating, (2) physical activity and reduced sitting, (3) smoking cessation, and (4) cardiac blues and depression. Participants in both the self-directed and supported arms are asked to complete modules relevant to them, in their own time and in any order over the course of 2 months. Within each module, participants undertake exercises that enable them to review situations in their lives, and using concepts from CBT, to identify, challenge, and change the unhelpful thoughts and beliefs associated with risk factors and negative emotions. Participants are prompted to develop action plans and coping plans for implementing practical health behaviors, including goal-setting, and identifying motivators for change, resources, barriers, rewards, and relapse prevention strategies. Other activities include using strategies to increase self-efficacy, including stories of role models, and exploring ratings of importance of and confidence to undertake behavior change.

The behavioral recommendations included in the modules (eg, healthy eating, physical activity, and smoking cessation) are all based on the current National Heart Foundation of Australia (NHFA) guidelines [52]. Although not being the central focus of the *Back on Track* program, it is important to present, up-to-date, relevant information on these guidelines and recommendations. This can help participants with aspects of their self-management, including goal-setting. Figures 2 and 3 show screenshots of various aspects of the web-based *Back on Track* modules.

**Figure 2 figure2:**
[figure not shown]
Examples of informative slides in the *Back on Track* program.

**Figure 3 figure3:**
[figure not shown]
Examples of interactive slides in the *Back on Track* program.

#### Additional Telephone Sessions for the Supported Group

Supported group participants are offered 2 telephone sessions with a trained lifestyle counselor to assist them in goal-setting and overall self-management while undertaking program modules. The session duration is 45-60 minutes for session 1 and up to 30 minutes for session 2. The first session occurs around 1-2 weeks postenrollment. The counselor begins the session with rapport development, then screens for anxiety and depression using the Patient Health Questionnaire-4 (PHQ-4) [53]. Self-efficacy for managing changes associated with health behaviors and emotional well-being is also assessed. Decisional balance and ambivalence are explored.

Motivational interviewing strategies are used to support participants to articulate clear and achievable goals and to identify areas they wish to address in behavioral and emotional self-management. Action and coping planning interventions are used to support translation of goals into actions. At completion of the first session, the second telephone session is scheduled for a mutually agreed time (approximately 4 weeks after the first session). The second telephone session includes a reflection on anxiety or depression symptoms, self-efficacy, coping and action plans, relapse prevention, and maintenance of behaviors. In addition, if the counselor considers that the individual requires more intensive mental health support, referral options for counseling are discussed.

An SMS reminder is sent 24 hours prior to each telephone session appointment to facilitate engagement. To ensure consistency and quality of program delivery, lifestyle counselors receive fortnightly supervision with an experienced registered health psychologist.

### Measures

Sociodemographic information is collected at baseline only. All participants complete the outcome measures of dietary intake, physical activity and sitting time, smoking status, anxiety and depression, stage of change, and self-efficacy in relation to behavioral and emotional self-management, quality of life, self-rated health, and well-being at baseline, post program (2 months after initial access to the program), and at 4-month follow-up (6 months after program access). Program acceptability is assessed post program only using a 6-item scale developed specifically for this study.

#### Primary Outcome Measures

##### Depression

Depression is assessed using the PHQ-9 [54]. The PHQ-9 is a brief 9-item depression screening tool based on the symptoms that comprise a diagnosis of major depressive disorder. Scores range from 0-27, with scores between 0-4 indicating minimal depression, 5-9, mild depression; 10-14, moderate depression; 15-19, moderately severe; and ≥20, severe depression. In patients with cardiac conditions, research has demonstrated an optimal PHQ-9 threshold of ≥6 [55,56], which combined improved sensitivity and retained specificity (sensitivity=83% and specificity=76% [56]) as compared to a threshold of ≥10, for detecting major depressive disorder based on a structured clinical interview. The PHQ-9 has been endorsed by the NHFA as the recommended tool for depression screening [57].

##### Physical Activity and Sitting Time

Physical activity and sitting time are measured using the Active Australia Survey (AAS) [58] with sitting questions from the International Physical Activity Questionnaire (IPAQ) (long form) [59]. The 8-item AAS measures frequency of walking, moderate activity, and vigorous activity in the last 2 weeks. The AAS has acceptable reliability and validity in the Australian community [60] and CR populations [61]. Participants are classified, according to the NHFA, as achieving the recommended target for adequate physical activity for secondary prevention [52] if they have been engaged in ≥150 minutes of physical activity per week combined across the 3 domains assessed. Sitting time is measured using the relevant questions from the IPAQ long form which asks participants about their total time spent sitting on a typical weekday and weekend day [59].

##### Dietary Intake

Diet quality is assessed using the Diet Quality Tool (DQT) [62], a 13-item questionnaire where all questions relate to nutrients of concern in the prevention of CVD (eg, fruit and vegetable, saturated fat, total fat, ω-3 fatty acids, fiber, and salt intake). Each item is scored from 0 to 10, where 10 indicates that the participant is meeting the NHFA’s secondary prevention nutrition guidelines [52]. Participants are classified as achieving a healthy diet for CHD secondary prevention if they receive a total DQT score >60%. This cut-off was originally identified by a panel of four accredited practicing dieticians with clinical, CR, and dietary research methodology experience, and validated against a 4-day food diary in Australian patients with cardiac conditions attending CR [62]. The DQT was found to be a valid and useful dietary assessment tool in a secondary CVD prevention setting [62].

#### Secondary Outcome Measures

##### Smoking Status

Smoking is assessed on the basis of self-reports by asking participants “Do you smoke?” Current smokers are asked how many cigarettes they smoke per day. Former smokers are asked when they quit smoking.

##### Anxiety

Anxiety is assessed using the 7-item Generalized Anxiety Disorder instrument (GAD-7) [63]. The GAD-7 was developed to provide a brief self-report measure to identify generalized anxiety in primary care, and asks participants, using 7-items, to indicate how often they have been bothered by certain problems over the past 2 weeks. The GAD-7 has good reliability and validity for detecting generalized anxiety [64]. The GAD-7 has been validated within a large sample of people in a primary care setting [63] and in cardiac populations [65].

##### Well-being

Well-being is assessed using the World Health Organization–Five Well-Being Index (WHO-5) [66]. This is a short, self-reported measure of current subjective mental well-being. The WHO-5 has adequate validity as an outcome measure in clinical trials and has been applied successfully as a generic scale for well-being across a wide range of study fields [67]. It has also been successfully used as a predictive tool for patients with cardiac conditions [68].

##### Quality of Life and Self-rated Health

Quality of life is measured using the Short Form Health Survey (SF-12) [69]. The SF-12 is a 12-item measure often used to compare health status between 2 groups of people, to identify predictors of health status and to determine health status in a specific disease population [70]. The SF-12 also includes one item that assesses self-rated health, which has been shown to predict survival [71]. The instrument is regarded as a reliable and valid generic measure of health-related quality of life in cardiac populations [72,73].

##### Self-efficacy

Self-efficacy is assessed using an 8-item scale, which has been designed specifically for this study. Participants indicate on a 5-point Likert scale how confident they are that they can make or sustain relevant behavioral and emotional changes.

##### Readiness to Change (Stages of Change)

Participants are asked to indicate their readiness to change relevant behaviors on a 5-point Likert scale from not thinking about making changes to have maintained changes for more than 6 months. This scale has been developed specifically for this study using wording from the Stages of Change model.

##### Additional Measures

Basic sociodemographic (namely age, sex, country of birth, marital status, living arrangement, employment status, educational level, and financial strain), medical (other physical and mental health conditions), and event-related information (event type, date of event, and attendance at cardiac rehabilitation) is collected via a self-report questionnaire, using standard questions used in previous ACHH studies [74].

### Data Analysis

In evaluating outcomes, there will be two groups of participants based on the mode of delivery: “self-directed” and “supported.” All statistical analyses will be performed on an intention-to-treat (ITT) basis with *P*<.05. In the case that ITT produces a null finding, it is possible that this is due to participants in the supported group not participating in the additional telephone sessions (that is, not receiving the intended treatment). To test that hypothesis, we will then undertake treatment-received analysis (also called Per Protocol) whereby only those who received the treatment in accordance with the protocol are included. This will enable us to determine whether any differences were obtained between those who received the self-directed treatment and those who received the supported treatment. *P* values less than .05 will be considered significant for the primary outcome and those less than .01 will be considered significant for secondary outcomes. The effect of the intervention on the primary and secondary outcomes at 6 months will be assessed using analysis of covariance (ANCOVA) models that include the baseline value of the outcome as a covariate and the group assignment (self-directed versus supported) as a categorical variable. The treatment effect, its effect size (Hedge g), and 95% CIs for the treatment effect and within-group changes from baseline to 6 months will be calculated from the ANCOVA models. The sensitivity of the results to missing data will be evaluated using a data-based multiple imputation procedure.

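### A per-protocol comparison that is run only after a null ITT result is presented as able to settle whether the two delivery modes differ

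*Protocol article*

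**What the plan says.** Four statements in Data Analysis belong together.

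- Basis: "All statistical analyses will be performed on an intention-to-treat (ITT) basis with" a .05 threshold.
- Trigger and presumed cause: "In the case that ITT produces a null finding, it is possible that this is due to participants in the supported group not participating", which refers to the calls.
- Selection: the article continues, "we will then undertake treatment-received analysis (also called Per Protocol) whereby only those who received the treatment in accordance with the protocol are included".
- Inference: "This will enable us to determine whether any differences were obtained between those who received the self-directed treatment and those who received the supported treatment".

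The section does not provide for this analysis when ITT is positive, attaches no alpha adjustment, does not call it supportive or exploratory, and does not reserve the conclusion for ITT.

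Two passages under Intervention show what could count as non-adherence. On calls: "Supported group participants are offered 2 telephone sessions with a trained lifestyle counselor". On modules: "Participants in both the self-directed and supported arms are asked to complete modules relevant to them, in their own time and in any order", with no minimum number.

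**The concern.** Two separate problems arise.

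First, an analysis done only after a null result is a second look at the same question at an unadjusted .05. It can add a positive finding but never remove one.

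Second, taking part in calls is behaviour after randomisation. In a behaviour-change trial, people who keep counseling appointments may well be those who would improve anyway. Comparing them with a self-directed arm that has not been selected in the same way can produce a difference with no effect of the calls. The analysis therefore cannot test the stated hypothesis that missed calls explain a null ITT result, because selection alone predicts the same pattern.

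What is at stake is the trial's purpose. Under Study Design, the comparison is meant to inform which delivery mode is rolled out across Australia.

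**Working it through.** **Inputs from the article.** Effect size 0.55, 80% power, threshold .05, 12% attrition, 60 per arm (Sample Size and Power); ANCOVA adjusted for the baseline value (Data Analysis). Two-sided testing is assumed.

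**The plan's own figure first.** n per arm = 2(1.96 + 0.84)² / 0.55² = 51.9, so 52. Dividing by 0.88 gives 59.1, so 60 per arm and 120 in total. The stated size is reproduced and is not in dispute. Evaluable per arm: 60 × 0.88 = 52.8, so 53 is used below.

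**Inputs the article does not give (assumptions).** Call completion c of 90%, 70% or 50%; correlation of motivation with completion s = 0.6; correlation of motivation with outcome r = 0.4 to 0.5; correlation of baseline with outcome 0.5.

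**Bias formula.** Suppose there is no treatment effect, completion follows a threshold on a normal latent variable, and motivation is unrelated to the baseline score. Dropping supported-arm non-completers then shifts that arm by r × s × φ(z)/c, where z cuts off the top share c of a standard normal. The factor φ(z)/c is 0.195 at 90%, 0.497 at 70% and 0.798 at 50%.

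- 90%: 0.24 × 0.195 = 0.05 to 0.30 × 0.195 = 0.06 SD
- 70%: 0.24 × 0.497 = 0.12 to 0.30 × 0.497 = 0.15 SD
- 50%: 0.24 × 0.798 = 0.19 to 0.30 × 0.798 = 0.24 SD

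**Simulation.** No true effect, 53 per arm, ANCOVA, ITT and then per-protocol, several thousand trials per setting:

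| Completion | Bias (SD) | ITT or per-protocol p < .05 |
|---|---|---|
| any, no selection | 0 | 6–8% |
| 90% | 0.05–0.06 | 7–8% |
| 70% | 0.12–0.15 | 11–15% |
| 50% | 0.19–0.24 | 17–24% |

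ITT alone stays at about 5%. The first row is the cost of the second look by itself.

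**If motivation also shows in the baseline score.** With a motivation–baseline correlation of 0.4 and r = 0.4, baseline adjustment leaves (0.4 − 0.5 × 0.4) × 0.6 × 0.497 = 0.06 SD at 70% and 0.2 × 0.6 × 0.798 = 0.10 SD at 50%. The simulated chance that either test is significant is then about 8% and 10%.

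**Scale.** Against the planned effect, 0.05/0.55 = 9% and 0.24/0.55 = 44%.

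**Limit.** The simulation uses a continuous outcome, whereas the article's main outcomes are proportions. It shows order of magnitude only.

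**The case against.** ITT is the stated basis of every analysis, and the second analysis is offered to explain a null result. Nothing says that it overrides ITT or counts as success. A reader might take the either-test rates as the trial's type I error. They are that only if a per-protocol result is accepted as evidence of benefit. This stands, and the figures are conditional on it. But the article does not exclude that use, and it claims more for the analysis than explanation.

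A reader might also infer that only the supported arm is filtered. The text does not say so: the rule has no arm limit, both arms are asked to complete relevant modules, and a detailed definition could sit in a plan not shown here. What remains is an inference from the written text, in which missed calls are the only non-adherence named and no criterion would exclude a self-directed participant.

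Nor is it established that bias could only favour support. The calls include screening for anxiety and depression and discussion of referral, and depression is a primary outcome. More distressed participants might be the likelier call-takers, which could reverse the bias for that outcome.

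Finally, treating treatment-received and per-protocol as the same thing is loose, since the first usually regroups non-recipients and the second drops them. The sentence goes on to describe dropping, so this is mainly a matter of terms.

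**Conclusion.** The point holds as a should-fix. The article states a wrong rule; this is not detail left to another document. A result-triggered analysis, conditioned on receipt of treatment after randomisation, is said to settle whether the treatments differ, and it cannot.

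If its result were accepted as evidence of benefit, the false-positive chance per outcome would be about 7% with no selection and about 7–24% across the assumed settings, with bias of about 0.05–0.24 SD. Completion and correlations are assumptions throughout. High completion, or a baseline score that captures motivation, brings the figures towards the lower end. The direction is plausibly towards support but not certain. The ITT estimate, the sample size and the randomised comparison itself are untouched, so no stronger rating is warranted.

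**What to change.** In Data Analysis:

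1. Delete the condition that ITT be null.
2. State that conclusions about supported versus self-directed delivery rest on ITT alone.
3. Define adherence in advance, report the adherence analysis whatever the ITT result, and label it supportive.
4. Replace the sentence claiming that it will establish whether the treatments differ with one saying that it describes the effect among those who took up the calls, under stated assumptions.

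Preferably, make it a complier average causal effect, with random assignment as instrument and the baseline score as covariate. Self-directed participants are not offered the calls, so non-receipt is one-sided and the method suits the question. It requires that assignment affects outcome only through the exposure as defined. Counting only completers of both calls as exposed would strain this, because someone who took the long first session may have benefited. Exposure such as at least one call received is more credible, and the assumption should be stated. For outcomes analysed as proportions, the same estimate can be given as a risk difference.

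The cost is a few lines of text and one extra model; call attendance should already be known to the counselors. The interval will be wider than a per-protocol one. Before baseline adjustment at an assumed 70% uptake, √(2/53)/0.7 = 0.28 against √(1/53 + 1/37) = 0.21 SD, about 30% wider. The estimate will not overturn a null ITT result. Simply running the per-protocol analysis unconditionally, labelled supportive, would be a cheaper but weaker repair, since the selection bias would remain.

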### Objectives

The aim of this study is to assess the benefits, in terms of behavioral and emotional well-being, of the web-based *Back on Track* self-management program, and to test whether participants obtain enhanced benefit through the provision of one-on-one telephone support from a trained lifestyle counselor (supported arm), over and above benefit obtained through completing the web-based program alone (self-directed arm). By including 2 follow-up assessments, one on postprogram completion (2 months) and one at 4 months post program (6 months postenrollment), we aim to assess both immediate and sustained benefits.

We hypothesize that participants randomly allocated to each arm of the trial will show significant improvement in their behavioral and emotional well-being, self-efficacy, and self-rated health from the preprogram to postprogram assessments, with benefits sustained 4 months after program completion. We also hypothesize that participants allocated to the supported program will demonstrate superior improvements in behavioral and emotional well-being, self-efficacy, and self-rated health compared to those allocated to the self-directed arm, at both the postprogram and follow-up assessments.

Ethical approval was granted by the Deakin University Human Research Ethics Committee (2019-438). This project has been funded by the HCF Research Foundation. This study will be conducted and reported in accordance with the CONSORT-EHEALTH guidelines [50].

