### Primary Outcome Measures: Depression, Physical Activity, and Dietary Intake

As the main outcomes, we will examine differences between the 2 groups in the proportion of participants who are:

classified as *nondepressed* at baseline, post program, and follow-up (based on a PHQ-9 score of <6) [55,56],achieving physical activity guidelines of ≥150 minutes of physical activity per week [52] at baseline, post program, and follow-up, orachieving healthy dietary guidelines of DQT scores >60% [62] at baseline, post program, and follow-up.

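### One .05 threshold is set for a single primary outcome, but three are named and no rule says how many must succeed or at which time point

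*Protocol article*

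**What the plan says.** All references are to the protocol article.

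- **Threshold.** Data Analysis opens with a general level of .05 ("All statistical analyses will be performed on an intention-to-treat (ITT) basis"). Later in the same paragraph it sets significance levels by tier: "values less than .05 will be considered significant for the primary outcome and those less than .01 will be considered significant for secondary outcomes". Here the primary outcome is in the singular.
- **Number of primaries.** The analysis subsection is headed "Primary Outcome Measures: Depression, Physical Activity, and Dietary Intake" and lists a proportion to be compared between arms for each of the three. The Measures section places the same three under its primary heading. One of its entries there is titled "Physical Activity and Sitting Time".
- **Time point.** Objectives hypothesises that the supported arm will do better "at both the postprogram and follow-up assessments". The list of primary analyses names baseline, post program and follow-up for each outcome. The ANCOVA in Data Analysis covers primary and secondary outcomes at 6 months only.
- **Sample size.** Sample Size and Power uses effect size 0.55, 80% power, threshold .05 and 12% attrition, giving 120 participants (60 per arm).
- **Use of the result.** Study Design says the comparison will inform how the program is delivered in a future national rollout.

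The article states no order of testing, alpha split, adjustment or joint success rule for the three primaries.

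**The concern.** The article does not simply leave error control to a later document. It fixes a level for each tier of outcome, tightens the secondary tier to .01, and leaves the primary tier at .05 as though it held one test. It holds three. Applied as written, the rule would let one P below .05 among the three be reported as primary success for counselor support, and that result is meant to guide rollout. The nominal 5% would then not describe the risk of a wrong decision. Because it is unclear whether 2 months is also a primary time point, the number of primary tests is not fixed either.

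**Working it through.** **1. Reproduce the plan's own figure.** Inputs from Sample Size and Power: d = 0.55, power 80%, alpha .05 (two-sided, not stated but it reproduces N), attrition 12%.

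- n per arm = 2 × ((1.960 + 0.842)/0.55)² = 51.9, so 52.
- 52/(1 − 0.12) = 59.1, so 60 per arm and 120 in total. This matches the plan.
- The calculation uses one test at .05, with no allowance for three outcomes.

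**2. Error rate for three tests at 6 months.** Assume all three nulls are true and any one P < .05 counts as success.

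- Independent tests: 1 − 0.95³ = 14.3%.
- The documents give no correlations between outcomes, so a range is assumed. Multivariate normal simulation (1,000,000 draws):

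| Correlation between outcomes | At least one false positive |
|---|---|
| 0 | 14.3% |
| 0.3 | 13.6% |
| 0.5 | 12.5% |
| 0.7 | 10.9% |

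**3. Error rate if the 2-month comparisons are also primary (3 outcomes × 2 visits = 6 tests).**

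- Independent tests: 1 − 0.95⁶ = 26.5%.
- Simulation with assumed correlations:

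| Between outcomes | Between visits, same outcome | At least one false positive |
|---|---|---|
| 0 | 0.5 | 24.9% |
| 0.2 | 0.6 | 23.6% |
| 0.3 | 0.7 | 22.0% |
| 0.5 | 0.8 | 19.0% |

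**4. Error rate if all primaries had to succeed.** It would be at most 5%, because a false claim would need every test to pass. The inflation in steps 2 and 3 therefore depends on the success rule that the article leaves open.

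**5. What control would cost.** Evaluable per arm: 60 × 0.88 = 52.8. The smallest of three P values under Holm is compared with .05/3 = .0167.

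- One named outcome, two-sample t test, d = 0.55: power 79.9% at .05 and 65.3% at .0167. The normal approximation has mean 0.55 × √(52.8/2) = 2.83, giving Φ(2.83 − 1.96) = 81% and Φ(2.83 − 2.39) = 67%.
- If all three true effects are 0.55, with correlation 0 to 0.7: power per outcome under the full Holm procedure is about 73-76%, and the chance of at least one significant primary is about 83-96%.

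These powers take the plan's d = 0.55 at face value as a standardised mean difference. They are not powers for the proportions listed as primary analyses.

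**The case against.** The strongest reply is that the article never says one significant primary is enough. The superiority hypothesis in Objectives is worded conjunctively, across domains and across both follow-ups. Read as a joint requirement, it would hold the error at or below 5%. The word joining the three proportions in the analysis list is weak evidence of a decision rule. This stands to the extent that the inflated rates are conditional. It does not remove the point: a hypothesis is not a success criterion, no joint rule is stated, and the stated threshold lets each primary be declared significant on its own.

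A reader might infer more than the text supports in four places.

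- **A flat error rate of 14-24%.** The documents do not establish this. It presumes that any one result suffices. Its upper end also needs 2 months to count as primary, which Objectives and the list of primary analyses suggest but the 6-month ANCOVA does not. That list names baseline too, so it may partly describe proportions over time.
- **Sitting time as a fourth primary.** It appears within a primary entry in Measures, but the analysis heading names exactly three outcomes. This is a loose end in labelling and does not support a four-test error rate.
- **A contradiction between .05 for everything and .01 for secondaries.** On an ordinary reading the specific sentence governs. It needs tidying only.
- **A 65% chance of any primary success after correction.** That figure is the power for one named outcome at .0167. It is not the chance that the smallest of three P values passes.

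Multiplicity procedures are often detailed in an analysis plan, which is not shown here. That defence is limited because the article itself fixes the primary level at .05.

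**Conclusion.** The point holds in conditional form. The article gives one .05 level to a single primary outcome, names three, and does not say how many must succeed or which time point decides. If any one significant primary counts as success, the false positive rate for the primary claim is about 11-14% at 6 months, and about 19-26% if the 2-month comparisons also count as primary. These figures assume that all nulls are true and use correlations that the documents do not give. Under the most favourable correlation shown, 6 months alone gives about twice the nominal level (10.9%). It should be settled before analysis, since the result is meant to inform rollout.

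**What to change.** - Name 6 months, already the ANCOVA time point, as the primary time point.
- Test depression, physical activity and diet there with Holm at an overall two-sided .05.
- Report the 2-month comparisons as secondary.
- Replace the general .05 statement with one saying that .05 applies to the primary family as a whole and .01 to the secondary outcomes.
- In Sample Size and Power, say that the 80% applies to a single outcome tested at .05.

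One named primary, or an explicit requirement that all three succeed, would also control the error. Holm keeps all three outcomes as primary and allows a claim on any of them.

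**Cost.** The text change is small and needs no new data. By the article's timeline, data collection runs to February 2022 with analysis afterwards, so the rule can be set before results are seen. The real cost is power: for one named outcome at d = 0.55 with 52.8 per arm it falls from about 80% to 65% at the strictest Holm step, or to about 73-76% per outcome if all three effects are 0.55. The chance of at least one significant primary would then be about 83-96%. Recruitment closed at 122, so a larger sample cannot make up the loss. The 2-month comparisons, part of the stated aim of showing immediate benefit, would be judged at .01.
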